### Design

This is a study protocol for a randomized, double-blind, placebo-controlled clinical trial with a treatment period of 12 weeks, which will be conducted between April 2019 and December 2020. Eligible patients will be randomized at a ratio of 1:1 into either the BBR group or the placebo group. The protocol was developed according to Consolidated Standards of Reporting Trials (CONSORT) statement [21], Standard Protocol Items: Recommendations for Interventional Trials (SPIRIT) 2013 [22], and SPIRIT 2013 explanation and elaboration: guidance for protocols of clinical trials [23]. A total of 4 visits will be scheduled at baseline (visit 1) and weeks 4 (visit 2), 8 (visit 3), and 12 (visit 4) to assess treatment efficacy, safety, and adverse events. This 12-week treatment period was set based on our clinical experience and previous pilot studies [13, 17]. Additionally, potential predictive factors involving patient and disease characteristics have been collected in a comprehensive manner. Figure 1 shows the flow diagram of the trial.

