#### Randomization

The stratified blocked randomization method will be used. The statistical software SAS 9.2 (SAS Institute Inc., Cary, USA) will be used by an independent statistician who is not involved in the implementation or statistical analysis of the trial. A random code list will be generated, and eligible participants will be randomly assigned to either the BBR group or the placebo group at a ratio of 1:1.

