### Outcomes

#### Primary outcome

The primary outcome is the percentage change in LDL-C from baseline at week 12.

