#### Sample size calculation

The sample size for this trial was calculated based on the primary outcome using the PASS 11.0 (NCSS LLC, Kaysville, UT, USA) software. According to the previous results of berberine on dyslipidemia [17, 26], the percentage reduction in LDL-C (the primary outcome) is 25% in the berberine group and 5% in the placebo group. Forty-seven patients in each group can achieve 80% power and rule out type I error of 5% by using a two-sided test. We expect that 20% of the participants may be lost to follow-up. Therefore, the sample size in each group should be adjusted to 59. In total, 118 participants will be enrolled in this trial.

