#### Statistical analysis

Statistical analysis of all data will be performed by a dedicated statistician in a blinded manner. All statistical analyses of the data will be performed using the SAS 6.12 (SAS Institute Inc., Cary, NC, USA) software.

The analysis data set will consist of a full analysis set (FAS), a per-protocol set (PPS), and a safety set (SS). FAS: according to the principle of analysis for intention to treat (ITT), participants will be rejected by the smallest and reasonable method. The last observation carried forward (LOCF) method will be used for the missing data supplement. The PP data set will include only participants who adhered to the study protocol and completed the clinical study. The minimum compliance rate for participants taking the investigational drugs in the PP data set is 80%. The SS will include information on safety records, including adverse events and laboratory test results. Quantitative indices recorded will include the numbers of cases, mean ± SD, median, and maximum and minimum values; qualitative or grade indices will be recorded using frequency and percentage. Two-sided tests will be used in all cases, and *P* ≤ 0.05 will be considered to be statistically significant.

From baseline to each time point, discrete variables will be described with frequencies and percentages, and continuous variables will be described with either mean and standard deviation for data with normal distribution or median and interquartile range for non-normally distributed data. For comparisons between the experimental and control groups at each time point, a chi-square test or Fisher’s exact test will be used for discrete variables, and Student’s *t* test or the Wilcoxon-Mann-Whitney *U* test will be used for continuous variables.

The analysis of concomitant medications will be analyzed by the chi-square test or Fisher’s exact test. The analysis of treatment compliance should include both the experimental drug and the basic treatment, and the chi-square test/Fisher exact probability method will be used for comparison.

All adverse events during the trial should be described in the form with the type, severity, and relationship with the experimental drug. Adverse events will be classified into all adverse events and related adverse events, among which, for conservative consideration, will include “definitely related,” “probably related,” “possibly related,” and “suspected related” to the drug.

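### The primary LDL-C comparison is an unadjusted t test or Wilcoxon test with no rule for choosing between them; it is valid, but it uses neither baseline LDL-C nor the randomisation strata and does not fix one primary test

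*Protocol article*

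**What the plan says.** - **Endpoint** (Protocol article, Primary outcome): "The primary outcome is the percentage change in LDL-C from baseline at week 12".
- **Test** (Statistical analysis): "For comparisons between the experimental and control groups at each time point", the article prescribes chi-square or Fisher tests for discrete variables, and "Student’s *t* test or the Wilcoxon-Mann-Whitney *U* test will be used for continuous variables". No separate method is given for the primary outcome. No covariate, ANCOVA, mixed model or stratified test appears anywhere in the article.
- **Choice between the two tests** (Statistical analysis): no rule is stated. The sentence just before concerns description only: "mean and standard deviation for data with normal distribution or median and interquartile range for non-normally distributed data". It suggests that the observed distribution would also decide the test, but the article does not say so.
- **Randomisation** (Randomization): "The stratified blocked randomization method will be used". The strata are not named in the article, and they play no part in the analysis it describes.
- **Baseline data** (Secondary outcomes; Table 1): LDL-C is measured at visit 1 in all participants.

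**The concern.** Expressing the outcome relative to baseline is not the same as adjusting for baseline. A patient whose visit 1 LDL-C happens to read high will tend to show a larger percentage fall in either arm, so percentage change usually stays negatively correlated with baseline. Three things follow.

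1. Variation that a covariate could explain is left in the error term, so the interval is wider than it need be.
2. If one arm starts with higher LDL-C by chance, the unadjusted difference moves in that arm's favour and nothing in the test corrects for it.
3. Stratifying the randomisation removes some between-arm variation. A test that ignores the strata does not credit this, so its standard error tends to be too large if the strata are prognostic.

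Separately, the t test compares means and the Wilcoxon test compares ranks. With both listed and no rule, the article does not say which result is the primary one.

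**Working it through.** **Inputs.** From Sample size calculation: "the percentage reduction in LDL-C (the primary outcome) is 25% in the berberine group and 5% in the placebo group", a 20-point difference; and "Forty-seven patients in each group can achieve 80% power and rule out type I error of 5% by using a two-sided test". Not in the document, so assumed over a range: the SD of percentage change, and r, its within-arm correlation with baseline LDL-C.

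**1. The plan's own figure.** No SD is stated, so 47 cannot be derived as a comparison of means. Treating 25% and 5% as two proportions (unpooled normal approximation) reproduces it:

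n = (0.25×0.75 + 0.05×0.95) × (1.960 + 0.842)² / 0.20² = 46.1, rounded up to 47 per arm. Then 47 / 0.8 = 58.75, rounded up to 59, or 118 in total.

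For a comparison of means, 47 per arm at 80% power corresponds to SD = 20 / (2.802 × √(2/47)) = 34.6 points. That SD is back-solved and is not a figure of the document, so smaller values are shown beside it.

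**2. Precision from adjustment.** Adjusted variance = (1 − r²) × unadjusted variance.

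| r | Variance saved | Equivalent extra patients, 1/(1 − r²) − 1 |
|---|---|---|
| 0 | 0% | 0% |
| 0.2 | 4% | 4% |
| 0.3 | 9% | 10% |

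Estimating one slope with 94 patients costs about 1/(94 − 4) = 1.1% of variance, so at r = 0 there is a trivial loss.

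**3. What that does to power at 47 per arm.** Power = Φ(20/SE − 1.96), with SE = SD × √(1 − r²) × √(2/47).

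| Assumed SD | r = 0 | r = 0.2 | r = 0.3 |
|---|---|---|---|
| 20 | 99.8% | 99.9% | 99.9% |
| 30 | 89.8% | 91.0% | 92.3% |
| 34.6 | 80.0% | 81.6% | 83.6% |

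**4. Chance imbalance.** An imbalance of z standard errors in baseline LDL-C moves the unadjusted difference by |r| × SD × z × √(2/47), where √(2/47) = 0.206.

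| Assumed SD | r | z = 1 | z = 1.96 |
|---|---|---|---|
| 20 | 0.2 | 0.8 points | 1.6 points |
| 20 | 0.3 | 1.2 points | 2.4 points |
| 34.6 | 0.2 | 1.4 points | 2.8 points |
| 34.6 | 0.3 | 2.1 points | 4.2 points |

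The assumed effect is 20 points.

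**5. A plausible r.** This was simulated with assumed true LDL-C of mean 3.4 to 4.3 mmol/L and SD 0.8, and with measurement variation of 11% at baseline and 15% at follow-up.

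- With no entry threshold, r was about −0.25 to −0.30.
- Keeping only baseline LDL-C of 4.1 mmol/L or more weakened it to about −0.15 to −0.21, a variance saving of about 2% to 5%.
- The inclusion criteria also admit patients on triglycerides alone. Letting in half of those below the LDL-C threshold gave r of about −0.28 to −0.30, a saving of about 8% to 9%.

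**6. Does an open choice of test disturb the error rate?** Simulation under the null used 47 per arm and 10,000 runs. A Shapiro normality pretest choosing between the two tests rejected in 5.1% of runs (normal data) and 4.7% (lognormal data).

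**The case against.** The strongest reply is that nothing here is invalid. A two-sample test on randomised groups is unbiased on average, and ignoring strata is at worst conservative. The endpoint already uses baseline as its denominator, and the analysis is to be done blinded. If the SD is well below 34.6, power against 20 points is already so high that a few percent of variance changes no decision. A rule for choosing the test, and the reporting of an interval, are details that an analysis plan not shown here may supply. Nor is it a fault that a condensed article does not name the strata.

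Most of that stands, and it rules out several stronger readings that a reader might infer:

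- **That the type I error is compromised.** The document does not support this. A normality pretest left the error at about 5%. Inflation, to 5.8% and 6.5% in the same simulation, appeared only when the smaller of the two p values was taken, which the article nowhere proposes.
- **That the data are stated to choose the test.** This is implied by the neighbouring sentence on description, not stated.
- **That the entry thresholds strengthen the dependence on baseline.** A threshold increases average regression to the mean, but it also restricts the baseline range, and the correlation weakened when it was applied.
- **That adjustment would be worth 20% to 25%.** A saving of that size needs r near 0.45. Nothing in the document supports such a value, and the simulated cases fall short of it.

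The reply does not remove the core. The article names a method for the primary outcome. That method is unadjusted and consists of two alternatives, so this is a stated choice and not a detail left out. Dividing by baseline does not replace adjusting for it.

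**Conclusion.** The point holds as an improvement to a valid analysis. The primary comparison is specified as either of two unadjusted tests. It gives up some precision, leaves chance imbalance in baseline LDL-C unadjusted in the test, makes no use of the stratification, and does not fix one primary test.

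The size is modest. With r between 0 and 0.3, the variance saving is 0% to 9%. It is probably only a few percent, and it stayed below a tenth in every case simulated. A 1.96-standard-error baseline imbalance would move the estimate by about 1.6 to 4.2 points for r of 0.2 to 0.3 and SD of 20 to 34.6. All of these figures rest on assumed SDs and correlations, because the document gives neither. What stratum adjustment would add cannot be estimated while the strata are unnamed. The lack of a single named primary test needs no assumption: it is on the face of the text.

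**What to change.** Replace the general rule, for the primary outcome, with one named analysis. Suggested wording:

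> The primary analysis is a linear model (ANCOVA) of percentage change in LDL-C from baseline to week 12, with treatment group, baseline LDL-C and the randomisation stratification factor(s) as terms. The result is the adjusted mean difference between berberine and placebo with its 95% confidence interval and two-sided p value. The Wilcoxon-Mann-Whitney test is a sensitivity analysis and does not replace the primary result.

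Take the stratification factors from the randomisation specification, so that the model matches what was done.

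The change costs wording in the protocol or analysis plan, settled before unblinding. It needs no new data, visits or patients.

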#### Protocol amendments

A formal amendment to the protocol will be required and must be approved by the major investigator and the Ethics Committee of the DHABUCM prior to implementation, if modifications may affect the conduct of the study, patients’ potential benefit or safety.

#### Monitoring and inspection

Data administrators should conduct regular monitoring to ensure that the data are adequately recorded in the case report forms and recorded prompt, accurate, and complete. The project management group will carry on conventional and emphasis inspection on every step of the research in order to evaluate whether the process of study is in accord with the protocol.

## Discussion

Several clinical studies of the efficacy of BBR in treating dyslipidemia have been published. A recent systematic review reported that the methodological quality of the majority of these trials was generally low in terms of random sequence generation, allocation concealment, blinding, and incomplete outcome data. Thus, selection bias, performance bias, detection bias, attrition bias, and confounding bias might exist [13]. Therefore, the evidence for the use of BBR in patients with dyslipidemia is not conclusive, and more rigorously designed studies with larger sample sizes are required. This is the study protocol of a randomized, double-blinded, placebo-controlled trial which aims to evaluate the efficacy and safety of BBR for dyslipidemia compared with placebo after 12 weeks of treatment. Our study will recruit a total of 118 participants to compare the effect of BBR with that of placebo in patients with dyslipidemia. The methods used for randomization, treatment concealment, and blinding are at low risk of bias and will be described in detail in the final report. The dose of BBR is 500 mg twice daily, within the range of active daily doses recommended by the consensus of the international lipid expert panel [27]. Furthermore, blood and stool samples will be kept to explore the potential lipid-lowering mechanism of BBR.

Meta-analysis showed that BBR could significantly reduce the levels of TC, LDL-C, and TG and also increase the level of HDL-C when used alone [27]. The lipid-lowering effect of BBR may be achieved through multiple mechanisms, including upregulating the expression of LDL-receptor (LDLR) [17], downregulating the expression of fat synthesis gene through activate adenosine monophosphate-activated protein kinase (AMPK) [28], downregulating the PPAR gamma gene [29], and increasing the activity of lipoprotein lipase (LPL) [30]. However, the main target of its lipid-lowering effect still needs further investigation.

### Trial status

This trial is currently recruiting patients. The recruitment process will be conducted between April 2019 and December 2020.

## Data Availability

All the individual participant data (text, tables, figures, and appendices) collected during the trial after deidentification will be available for anyone who wishes to access the data immediately following publication in accordance with the FAIR principles.

## Abbreviations

ALT: Alanine transaminase
AMPK: AMP-dependent protein kinase
AST: Aspartate aminotransferase
BBR: Berberine
BP: Blood pressure
BUN: Urea nitrogen
BSC: Bristol Stool Chart
CRF: Case report form
Cr: Creatinine
DHABUCM: Dongzhimen Hospital Affiliated to Beijing University of Chinese Medicine
FAS: Full analysis set
HDL-C: High-density lipoprotein cholesterol
hs-CRP: High-sensitivity C-reactive protein
LDL-C: Low-density lipoprotein cholesterol
LDLR: LDL receptor
LLDs: Lipid-lowering drugs
LPL: Lipoprotein lipase
PPS: Per-protocol set
SS: Safety set
TC: Total cholesterol
TCM: Traditional Chinese medicine
TG: Triglyceride
